## Introduction

Asthma has a high prevalence worldwide with a high incidence in primary care settings in many countries.^1^ It is by definition a variable disease with a broad spectrum of clinical phenotypes, in which management and treatment can be difficult.^2–8^ The aim of asthma treatment is optimal control of the disease, which according to Global Initiative for Asthma (GINA) guidelines implies both symptom control and prevention of exacerbations.^1^ Despite several treatment options, studies show that about half of the patients have poor asthma control.^2,3^ When asthma is not controlled, it decreases the quality of life, increases the risk of exacerbations and premature death and is a high cost for the society.^2,3^

There are concerns that current asthma treatment is based on research with subjects who are not representative of the patients seen in clinical practice.^9^ Guidelines for the management of asthma are usually developed on the basis of the available empirical evidence, and particular emphasis is placed on the conclusions of randomised controlled clinical trials (RCTs) and meta-analyses of RCTs that have been placed at the top of the evidence hierarchy.^10^ However, most RCTs have restricted inclusion criteria to obtain a high level of internal validity and usually recruit patients from secondary health-care settings. The external validity of RCTs, which provides evidence for major clinical guidelines, may be questioned if they are not representative of real-life populations in primary care.^11–15^ In the 2007 study by Travers *et al*, only 4% (range 0–36%) of participants with asthma in a population-based survey met the eligibility criteria to be included in 17 major RCTs cited in the GINA guidelines.^14^ The same study found that only 6% (range 0–43%) of participants receiving asthma treatment also met the eligibility criteria. The proportion of patients with asthma from primary care settings that would be eligible for the major RCTs is unknown. If the proportion is similar to that found in the study by Travis *et al.*, then the generalisability of the conclusions and the clinical relevance of major RCTs may be questionable, and they have not been improved in the past decade. There is a need to explore the external validity of pharmacological RCTs in primary care populations. The UNLOCK (Uncovering and Noting Long-Term Outcomes in COPD and asthma to enhance knowledge) project^15^ of the International Primary Care Respiratory Group (IPCRG) covers a broad primary care population that may help clarify the external validity of these RCTs.

## Aims and objectives

The aim of this study is to determine whether the inclusion criteria for patients with asthma in the major RTCs supporting GINA guidelines are representative of real-life primary care populations with asthma. The study will address the following research questions:

What proportion of patients in primary care would be eligible for the major RCTs assessing patients at treatment step two heading for step three?What are the clinical characteristics of these patients when compared with participants in major RCT studies?

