This study will provide estimates of the proportion of real-life primary care populations that are eligible for RCTs. It will also present descriptive characteristics of primary care patients compared with patients included in RCTs. This will present relevant information for the adequacy and use of GINA and other major guidelines in primary health-care settings.^16–20^ Previous findings suggest that the level of representation of the population with asthma^14^ and chronic obstructive pulmonary disease (COPD)^13^ in RCTs may be lower than desirable. This study can inform not only the development of future clinical practice guidelines^17–20^ but also the way asthma clinical trials are being designed and implemented.^10^ The study will tell us more about the patients who are not eligible for these major RCTs, and it may also provide new insights into why the control of asthma in many patients does not appear to improve in spite of the implementation of the treatment strategies that are recommended in guidelines.

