### Data collection and inclusion criteria

Data collection will involve two steps:

Step one will identify the major relevant RCTs used in GINA guidelines.Step two will identify the primary care data sets that contain the required variables to assess eligibility for participation in the major RCTs.

In step one, a Systematic Review focusing the search on selected asthma international guidelines (i.e., GINA) will be conducted in order to identify all studies that fit the following criteria:

Randomised controlled clinical trialPharmacological treatment at GINA management step 2 heading for step 3RCT sample size *n*>400Other criteria (e.g., mainly adult population)

The systematic review will follow the PRISMA^21^ statement guidelines and follow the steps identified in Figure 1.

In step two, members of the IPCRG UNLOCK group will be invited to participate in the study with primary care data sets that include the variables listed in Table 1.

Participants identified in the data sets will remain anonymous. Patient confidentiality will be assured in the collection and merging of the data sets.

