## Figures and Tables

**Figure 1 fig1:**
[figure not shown]
Flowchart of RCT identification process.

**Table 1 tbl1:** List of variables for data set inclusion in the study

*Variables*	*Required*	*Optional*
Age (>12 years)	√	
Gender	√	
Medication: ICS, LABA, SABA, combination, Montelukast—(last 3 months) fixed combination (ICS/LABA)	√	
*One of:*		
Asthma control (GINA or ACQ or ACT)	√	
QoL (miniAQLQ)		
		
Smoking history: (never–former–current)		√
		
*Latest lung function assessment*		
FEV_1_ % of predicted		√
FEV_1_ reversibilty		
FEV_1_/FVC (VC) ratio		
		
Allergy (pollen, pets, house dust mite)		√
Allergic rhinitis		√
Comorbidities heart disease (i.e., heart failure or ischaemic heart disease)		√
Asthma control (i.e., according to GINA: last week: daytime symptoms, night symptoms rescue medication and exacerbations history, courses of oral steroids history or ACQ or ACT)		√
QoL (i.e., miniAQLQ)		

Abbreviations: ACQ, asthma control ouestionnaire; ACT, asthma control test; ICS, inhaled corticosteroids; LABA, long-acting β-agonists; miniAQLQ, mini quality of life questionnaire; QoL, quality of life; SABA, short-acting β-agonists.

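### Eligibility for step 2-to-3 trials is measured over primary care patients with no stated step limit, so a low proportion could reflect the study's own trial filter

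*Protocol article*

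**What the plan says.** Under Aims and objectives, the article asks whether the inclusion criteria of the main trials behind the GINA guidelines "are representative of real-life primary care populations with asthma". Research question 1 turns this into a proportion: "What proportion of patients in primary care would be eligible for the major RCTs assessing patients at treatment step two heading for step three". The Discussion promises the same quantity in broader terms: "This study will provide estimates of the proportion of real-life primary care populations that are eligible for RCTs".

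Data collection and inclusion criteria then restricts the trials. They must be randomised, concern drug treatment at the step 2-to-3 transition and have more than 400 participants. A mainly adult population is given as an example of further criteria. On the patient side, group members are invited to join "with primary care data sets that include the variables listed in Table 1". Table 1 lists age above 12 years, gender and recent medication as required, with one of asthma control or quality of life. It states no treatment-step rule. Data analysis promises descriptive statistics and proportions and names no narrower denominator.

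The Introduction supplies the benchmark. For 17 major trials cited in GINA, "only 4% (range 0–36%) of participants with asthma in a population-based survey met the eligibility criteria", and "only 6% (range 0–43%) of participants receiving asthma treatment also met the eligibility criteria". It says that a similar proportion in primary care would cast doubt on how far the conclusions of the main trials apply.

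**The concern.** Numerator and denominator are set on different populations. The numerator counts patients who fit trials of one treatment transition. The denominator, as worded, is patients with asthma in primary care, whatever their step. A patient on no controller treatment, or one already above step 2, may fail every selected trial only because trials for that patient's step were never selected. Such a failure says nothing about whether the evidence behind GINA represents that patient, since other GINA-cited trials may do so.

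The ratio therefore mixes two causes: restrictive trial criteria, which the aim is about, and the study's own choice of trials. The Introduction has already said how a low figure will be read, namely against a benchmark from 17 GINA trials for which it states no step restriction. The Discussion also plans to learn about patients who are not eligible and to draw insight into poor asthma control. That group could contain many patients whom the selected trials were never meant to serve.

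**Working it through.** The document gives no sample size, power or target precision, so there is no figure of the plan's own to reproduce. The check has two parts.

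**1. The texts side by side**

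| Element | Where | Step limit? |
|---|---|---|
| Aim | Aims and objectives | None |
| Patients in research question 1 | Aims and objectives | None; the step phrase describes the trials |
| Planned estimate | Discussion | None |
| Trials selected | Data collection and inclusion criteria | Step 2-to-3 only |
| Data sets admitted | Data collection and inclusion criteria; Table 1 | None |
| Analysis | Data analysis | None stated |

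Only the trial side is restricted.

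**2. What this does to the proportion**

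Inputs, none of which the document gives:
- s: share of patients at the step the trials target (assumed 20% to 80%).
- e: eligibility within that group (assumed 20% for illustration).
- e₀: eligibility among patients at other steps.

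Proportion over all patients: P = s × e + (1 − s) × e₀.

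If e₀ = 0, then P = s × e. Since e is at most 1, P cannot exceed s, however permissive the trials' other criteria are.

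With e = 20% and e₀ = 0:

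| s | P = s × 0.20 | Ceiling on P |
|---|---|---|
| 20% | 4% | 20% |
| 40% | 8% | 40% |
| 60% | 12% | 60% |
| 80% | 16% | 80% |

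The same within-step eligibility of 20% thus gives an all-patient figure between 4% and 16%. At s = 20% it equals the 4% benchmark in the Introduction, although eligibility among relevant patients is five times higher (20/4 = 5).

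In reverse, e = P/s. An observed 6% corresponds to 6/0.2 = 30% of relevant patients at s = 20%, 6/0.4 = 15% at s = 40%, and 6/0.8 = 7.5% at s = 80%.

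The dilution shrinks if some patients at other steps do qualify. For example, with e₀ = 10% and s = 40%, P = 0.4 × 0.20 + 0.6 × 0.10 = 14%, against 8% with e₀ = 0.

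The background figures also show that the denominator matters: 4% of participants with asthma against 6% of those on treatment, a ratio of 6/4 = 1.5. They come from another study and do not predict this one.

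**The case against.** The strongest reply is that the denominator is open rather than wrong. Nowhere does the article say that all patients at any step will be counted. Table 1 governs which data sets may enter, not who is counted in question 1. Its required items, medication plus control or quality of life, suit finding patients treated at step 2 who might step up. The step limit on the trials is disclosed in the research question itself. A condensed article may leave denominators and stratified reporting to a fuller document.

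Part of this stands. A reader might infer that the plan fixes its denominator as every asthma patient older than 12 at any step. The document does not support that: it leaves the patient side unrestricted but does not say so outright. A reader might also infer a definite size, such as a cap of 20% to 40%. No share at the target step is given, at a share of 80% the cap matters much less, and no selected trial's criteria are shown, so zero eligibility at other steps is itself an assumption. Likewise, one might infer that adolescents are excluded by design. The mainly adult criterion is only an example and allows trials that admit adolescents, so age matters only where a selected trial enrols adults only.

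What does not stand is that this is merely omitted detail. The aim, question 1 and the Discussion all word the patient side without a step limit, and the selection rule imposes one on the trials. An analysis plan that silently narrowed the denominator would answer a different question from the one published.

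**Conclusion.** The concern holds as a mismatch between the stated question and the trial selection rule. Followed as written, the main proportion cannot separate restrictive trial criteria from the study's own filter, so a low value would not by itself support the inference the Introduction prepares.

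The size cannot be fixed from the document. The bound P ≤ s holds if patients at other steps are all ineligible. The 4% to 16% range further assumes 20% eligibility within the target step and shares of 20% to 80%. Age is a secondary issue.

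This should be corrected before analysis, but it is not a fatal flaw. The study is descriptive, medication is required in every data set, and the repair needs no new design.

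**What to change.** - Using the required medication data, report as the main result the eligible proportion among patients at the treatment step the selected trials target and within each trial's own age range.
- Add control status to that definition only where the data set records it. Table 1 appears to accept quality of life as an alternative, so it cannot be required everywhere.
- Report the proportion among all asthma patients in the data sets as a second figure, labelled as such.
- Split ineligibility into two parts: a different treatment step or age, and other eligibility criteria.
- Limit the aim and the conclusion to trials supporting the step 2-to-3 transition, and make the comparison with the earlier survey subject to the same limit.

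The cost is revised wording and one further stratification. The step-matched denominator will be smaller and its estimates less precise. Assigning step from medication is approximate, so the rule used should be stated.

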## Discussion

Asthma is a highly prevalent disease worldwide with variability and a large range of phenotypes.^1–8^ The management and treatment of patients with asthma in primary care is a challenge, and many patients still suffer from poor asthma control.^2^ The major international clinical guidelines for the prevention and management of asthma are influenced by the empirical evidence and conclusions of RCTs.^9–14^ However, RCTs tend to be highly selective in terms of inclusion and exclusion criteria for people with asthma and may under-represent primary care populations with asthma. Smokers, for example, are usually excluded from registration RCTs assessing inhaled corticosteroids (ICS), as smoking is known to reduce the efficacy of ICS.^16^ Other common exclusion criteria are pregnancy, lactation, elderly patients and other chronic diseases such as ischaemic heart disease. A common inclusion criterion is a bronchodilator FEV_1_ reversibility of 12 or 15%, which is not a frequent clinical sign in real-life asthma patients, and in the Travers study, 71 (or 76%) of participants with asthma were excluded.^14^

RCTs are important in establishing the efficacy and short-term safety of new therapies, but there are limitations in evaluation of effectiveness of the therapies in the real world.^17^ The assessment of the external validity of asthma RCTs is therefore needed to better understand the clinical relevance of their conclusions. There should be discussion on the need for effective studies, pragmatic trials and observational studies, as a complement to RCTs, to evaluate treatment outcomes in real-life clinical settings including the whole asthma population. The main weakness of these studies might be a lower internal validity, which needs to be addressed in the design of the studies. When developing guideline recommendations in the future, data from both efficacy and effectiveness studies should be evaluated with the strengths and weaknesses given.^18^

This study will provide estimates of the proportion of real-life primary care populations that are eligible for RCTs. It will also present descriptive characteristics of primary care patients compared with patients included in RCTs. This will present relevant information for the adequacy and use of GINA and other major guidelines in primary health-care settings.^16–20^ Previous findings suggest that the level of representation of the population with asthma^14^ and chronic obstructive pulmonary disease (COPD)^13^ in RCTs may be lower than desirable. This study can inform not only the development of future clinical practice guidelines^17–20^ but also the way asthma clinical trials are being designed and implemented.^10^ The study will tell us more about the patients who are not eligible for these major RCTs, and it may also provide new insights into why the control of asthma in many patients does not appear to improve in spite of the implementation of the treatment strategies that are recommended in guidelines.

## Materials and methods

### Study design

The study will use an observational design for comparing baseline characteristics of asthma patients in primary care databases with the inclusion criteria in the pharmacological RCTs that support major international guidelines (i.e., GINA).

### Data collection and inclusion criteria

Data collection will involve two steps:

Step one will identify the major relevant RCTs used in GINA guidelines.Step two will identify the primary care data sets that contain the required variables to assess eligibility for participation in the major RCTs.

In step one, a Systematic Review focusing the search on selected asthma international guidelines (i.e., GINA) will be conducted in order to identify all studies that fit the following criteria:

Randomised controlled clinical trialPharmacological treatment at GINA management step 2 heading for step 3RCT sample size *n*>400Other criteria (e.g., mainly adult population)

The systematic review will follow the PRISMA^21^ statement guidelines and follow the steps identified in Figure 1.

In step two, members of the IPCRG UNLOCK group will be invited to participate in the study with primary care data sets that include the variables listed in Table 1.

Participants identified in the data sets will remain anonymous. Patient confidentiality will be assured in the collection and merging of the data sets.

### Data analysis

Data will be analysed according the defined criteria for the identification of RCTs. Statistical analysis of the data sets will provide summary descriptive statistics, means, measures of dispersion and proportions. The statistical analysis will focus on group classification values, and no individual statistical values will be computed or revealed.

### Ethical approval

All included data sets will require approval by local primary care research ethics committees.

## Figures and Tables

**Figure 1 fig1:**
[figure not shown]
Flowchart of RCT identification process.

**Table 1 tbl1:** List of variables for data set inclusion in the study

*Variables*	*Required*	*Optional*
Age (>12 years)	√	
Gender	√	
Medication: ICS, LABA, SABA, combination, Montelukast—(last 3 months) fixed combination (ICS/LABA)	√	
*One of:*		
Asthma control (GINA or ACQ or ACT)	√	
QoL (miniAQLQ)		
		
Smoking history: (never–former–current)		√
		
*Latest lung function assessment*		
FEV_1_ % of predicted		√
FEV_1_ reversibilty		
FEV_1_/FVC (VC) ratio		
		
Allergy (pollen, pets, house dust mite)		√
Allergic rhinitis		√
Comorbidities heart disease (i.e., heart failure or ischaemic heart disease)		√
Asthma control (i.e., according to GINA: last week: daytime symptoms, night symptoms rescue medication and exacerbations history, courses of oral steroids history or ACQ or ACT)		√
QoL (i.e., miniAQLQ)		

Abbreviations: ACQ, asthma control ouestionnaire; ACT, asthma control test; ICS, inhaled corticosteroids; LABA, long-acting β-agonists; miniAQLQ, mini quality of life questionnaire; QoL, quality of life; SABA, short-acting β-agonists.

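### Table 1 admits data sets that hold a quality-of-life score but no asthma control measure, so any control criterion of a selected RCT cannot be applied in them

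*Protocol article*

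**What the plan says.** Research question 1, under Aims and objectives, asks "What proportion of patients in primary care would be eligible for the major RCTs assessing patients at treatment step two heading for step three".

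The section Data collection and inclusion criteria describes how data sets are chosen: "Step two will identify the primary care data sets that contain the required variables to assess eligibility for participation in the major RCTs". It then invites group members to take part with "primary care data sets that include the variables listed in Table 1".

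Table 1 marks age, gender and recent medication as required. The medication row reads "Medication: ICS, LABA, SABA, combination, Montelukast—(last 3 months) fixed combination (ICS/LABA"). Below it is a block headed as a choice of one, with two rows:

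- "Asthma control (GINA or ACQ or ACT"), which carries the Required tick;
- QoL by miniAQLQ, with no tick.

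Near the foot of the table control appears again, this time with the Optional tick: "Asthma control (i.e., according to GINA: last week: daytime symptoms, night symptoms rescue medication and exacerbations history". QoL follows it, again without a tick of its own.

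**The concern.** Table 1 is the gate for data sets, and its required part is meant to be enough to judge eligibility for the RCTs. If miniAQLQ alone satisfies the either/or block, a data set can pass with no asthma control measure at all. The article does not say how a miniAQLQ score would stand in for control.

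What is at stake is the proportion in research question 1. Where an RCT selects patients partly on control, that criterion could be applied in some data sets and not in others, and the proportions would then rest on different sets of criteria. An analysis plan, however detailed, cannot supply a variable that the data set does not hold.

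**Working it through.** There is no stated figure to reproduce: the study is descriptive ("Statistical analysis of the data sets will provide summary descriptive statistics, means, measures of dispersion and proportions"). The check is a reading of Table 1 against the entry rule and research question 1.

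**1. Does the table allow miniAQLQ alone?** Three features bear on this.

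- The block is headed as a choice of one, which would be idle if only one row could satisfy it.
- The tick is on the first row only. The lung function block shows the same pattern, with one tick for three rows, so the blank beside QoL is probably a merged cell.
- Asthma control is listed again as optional, which makes sense only if it is not always required.

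The either/or reading is therefore the more natural one. If control was meant to be mandatory, the table marks the same item as both required and optional. The two entries need reconciling in either case.

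**2. What is the smallest data set that can enter?** Age, gender, medication class in the last 3 months, and miniAQLQ. Symptoms, exacerbation history and oral steroid courses appear in Table 1 only as parts of the optional asthma control entry.

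**3. What can that data set show?** Medication class may suggest the current treatment step. The row lists neither dose nor control status. A control criterion in a selected RCT therefore has nothing in the data to be tested against.

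**4. Which way does the estimate move?** Take one RCT with a control criterion and one data set of N patients.

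- Let A be the number who meet all the RCT's other criteria.
- Let B be the number among those A who also meet the control criterion, so B ≤ A.
- The correct proportion is B/N. If the control criterion is ignored, the result is A/N.
- Since B ≤ A, A/N ≥ B/N. The estimate stays the same or is too high, whichever level of control the RCT asks for.
- The ratio of the two is A/B, that is, 1 divided by the share of otherwise eligible patients who meet the control criterion.

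**5. Can the ratio be filled in?** No. The article does not give that share. The RCTs have still to be identified, so their control criteria are not known, and the number of data sets with miniAQLQ but no control measure is not stated.

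**The case against.** The case on the other side has several parts.

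*The table reading is an inference.* The Required tick does sit on the control row, and the table may have lost merged cells in extraction. This stands as a caution. It does not remove the point, because the alternative reading leaves control both required and optional.

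*The step-two-to-three phrase describes the RCTs.* It appears as a criterion for choosing RCTs, and Study design says patients are to be set against the RCTs' inclusion criteria. A reader might infer that every data set must classify each patient as moving from step two towards step three. The article states no such patient-level filter, so the point is confined to RCTs that have a control criterion.

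*Nothing says that an untested criterion counts as met.* This is correct. A reader might infer that well-controlled patients will be counted as eligible, but the article does not state how criteria that cannot be assessed are handled, and that may be set out in a fuller document. The upward direction therefore holds only if the criterion is ignored. Other handling would also have a price: treating it as failed would give zero eligible patients for that RCT in that data set, and leaving the data set out would make its entry pointless for research question 1.

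*Three control instruments are accepted.* A reader might infer that GINA, ACQ and ACT will be treated as interchangeable. Table 1 lists them as alternatives for entry, and no section says their scores are pooled or equated. Data analysis speaks of group classifications, which fits a category of control defined within each instrument.

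*Other selection variables are optional too.* The Discussion names smoking, reversibility and heart disease as common grounds for selection, and Table 1 makes all three optional. This stands: requiring control would not by itself make the proportions comparable across data sets. It closes one gap, in the one block that the table itself treats as required.

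**Conclusion.** The point holds as a flaw in the entry rule. On its natural reading, Table 1 admits data sets without any asthma control measure, although the required variables are meant to support the judgement of RCT eligibility. In those data sets a control criterion cannot be applied. If it is ignored, the eligible proportion is unchanged or too high, and the RCTs would look at least as representative as they are.

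This rests on three conditions: that at least one selected RCT has a control criterion, that at least one participating data set supplies miniAQLQ without control, and, for the direction, that the untested criterion is passed over.

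No size can be given. A reader might take the Introduction's remark that about half of patients have poor control and infer a doubling, 1/0.5 = 2. The documents do not support that. The remark concerns asthma patients in general and not those otherwise eligible. The doubling would also need every RCT to require poor control, control to be independent of the other criteria, and untested patients to be counted as eligible.

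The point should be settled before data sets are admitted. It does not undermine the descriptive comparison in research question 2.

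**What to change.** In Table 1, require an asthma control measure (GINA, ACQ or ACT) for any data set that contributes to the eligibility proportion in research question 1. Delete the second, optional entry for asthma control, or reword it so that it covers only additional detail and no longer conflicts with the required one. Make miniAQLQ an addition and not a substitute, and keep data sets with quality of life only for the descriptive comparison in research question 2.

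The cost is an edit to one table and the loss of those data sets from the eligibility estimate. How many would be lost cannot be told from the article.
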